***Appendix 5. Cabinda Study Questionnaire***

## **Appendix 6. RDS Non-response Assessment Form**

### **RDS Non-response Assessment Form**

(This form will be translated and back-translated by different translators to Portuguese.)

#### **BIOBEHAVIORAL SURVEY IN CABINDA**

**Instructions:** Collect this information face-to-face from returning recruiters each time they come to collect their compensation.

**Oral consent script:** I am going to ask you a few questions about the people you tried to recruit with your coupons for this survey. We ask because we are especially interested in knowing about people who say they do not want a coupon. I do not want to know anyone's name, not even yours, for these questions. May I continue?

Coupon Identification Number: |\_\_|\_\_|\_\_|\_\_|\_\_|\_\_|\_\_|\_\_|\_\_|\_\_|

Name of Interviewer: \_\_\_\_\_ Date of Interview: \_\_\_\_\_

1. Is this the first time you have been here to collect compensation? Yes\_\_\_\_\_ No\_\_\_\_\_

If yes, continue. If no, answer questions for the period of time between when the subject was last here and filled out this same questionnaire and now.

2. How many coupons did you give out? \_\_\_\_\_ (Between the last time you came here to receive compensation and now).

3. How many people refused to accept coupons? \_\_\_\_\_ (if zero, skip to question 5. If > zero, continue)

4. These questions are asked for each individual who refused to accept the coupon.

|                                                                                                                                                                                       | Person 1                                                                                                                                                                                                                                                                                                                                                                                                | Person 2                                                                                                                                                                                                                                                                                                                                                                                                | Person 3                                                                                                                                                                                                                                                                                                                                                                                                | Person 4                                                                                                                                                                                                                                                                                                                                                                                                |
|---------------------------------------------------------------------------------------------------------------------------------------------------------------------------------------|---------------------------------------------------------------------------------------------------------------------------------------------------------------------------------------------------------------------------------------------------------------------------------------------------------------------------------------------------------------------------------------------------------|---------------------------------------------------------------------------------------------------------------------------------------------------------------------------------------------------------------------------------------------------------------------------------------------------------------------------------------------------------------------------------------------------------|---------------------------------------------------------------------------------------------------------------------------------------------------------------------------------------------------------------------------------------------------------------------------------------------------------------------------------------------------------------------------------------------------------|---------------------------------------------------------------------------------------------------------------------------------------------------------------------------------------------------------------------------------------------------------------------------------------------------------------------------------------------------------------------------------------------------------|
| 1. What is your relationship to this person (Check all that apply)                                                                                                                    |  1. A stranger, someone you met for the first time
 2. Someone you knew, but not closely
 3. A close friend, someone you knew very well
 4. A sexual partner
 5. A family member
 6. A dealer
 7. Other _____ |  1. A stranger, someone you met for the first time
 2. Someone you knew, but not closely
 3. A close friend, someone you knew very well
 4. A sexual partner
 5. A family member
 6. A dealer
 7. Other _____ |  1. A stranger, someone you met for the first time
 2. Someone you knew, but not closely
 3. A close friend, someone you knew very well
 4. A sexual partner
 5. A family member
 6. A dealer
 7. Other _____ |  1. A stranger, someone you met for the first time
 2. Someone you knew, but not closely
 3. A close friend, someone you knew very well
 4. A sexual partner
 5. A family member
 6. A dealer
 7. Other _____ |
| 2. How long have you known this person?                                                                                                                                               |  1. Less than 6 months
 2. 6 months to 1 year
 3. 1-2 years
 4. 3-6 years
 5. More than 6 years                                                                                                                                                                     |  1. Less than 6 months
 2. 6 months to 1 year
 3. 1-2 years
 4. 3-6 years
 5. More than 6 years                                                                                                                                                                     |  1. Less than 6 months
 2. 6 months to 1 year
 3. 1-2 years
 4. 3-6 years
 5. More than 6 years                                                                                                                                                                     |  1. Less than 6 months
 2. 6 months to 1 year
 3. 1-2 years
 4. 3-6 years
 5. More than 6 years                                                                                                                                                                     |
| 3. What was the main reason given for refusing to accept a coupon?

(Do not read. Ask for each individual who refused to accept the coupon)

Check all that apply. |  1. Too busy
 2. Already had a coupon
 3. Already participated in survey
 4. Younger than 18
 6. Not resident of _____
 7. Fear of being identified as _____
 8. Site is too far away                         |  1. Too busy
 2. Already had a coupon
 3. Already participated in survey
 4. Younger than 18
 6. Not resident of _____
 7. Fear of being identified as _____
 8. Site is too far away                         |  1. Too busy
 2. Already had a coupon
 3. Already participated in survey
 4. Younger than 18
 6. Not resident of _____
 7. Fear of being identified as _____
 8. Site is too far away                         |  1. Too busy
 2. Already had a coupon
 3. Already participated in survey
 4. Younger than 18
 6. Not resident of _____
 7. Fear of being identified as _____
 8. Site is too far away                         |

|  |                                                                                                                                                        |                                                                                                                                                        |                                                                                                                                                        |                                                                                                                                                        |
|--|--------------------------------------------------------------------------------------------------------------------------------------------------------|--------------------------------------------------------------------------------------------------------------------------------------------------------|--------------------------------------------------------------------------------------------------------------------------------------------------------|--------------------------------------------------------------------------------------------------------------------------------------------------------|
|  |  9. Not interested
 10. Incentive is not worth the time
 11. Other _____ |  9. Not interested
 10. Incentive is not worth the time
 11. Other _____ |  9. Not interested
 10. Incentive is not worth the time
 11. Other _____ |  9. Not interested
 10. Incentive is not worth the time
 11. Other _____ |
|--|--------------------------------------------------------------------------------------------------------------------------------------------------------|--------------------------------------------------------------------------------------------------------------------------------------------------------|--------------------------------------------------------------------------------------------------------------------------------------------------------|--------------------------------------------------------------------------------------------------------------------------------------------------------|

5. Of those people who accepted a coupon:

|                                                                                       | Person 1                                                                                                                                                                                                                                                                                                                                                                                                | Person 2                                                                                                                                                                                                                                                                                                                                                                                                | Person 3                                                                                                                                                                                                                                                                                                                                                                                                |
|---------------------------------------------------------------------------------------|---------------------------------------------------------------------------------------------------------------------------------------------------------------------------------------------------------------------------------------------------------------------------------------------------------------------------------------------------------------------------------------------------------|---------------------------------------------------------------------------------------------------------------------------------------------------------------------------------------------------------------------------------------------------------------------------------------------------------------------------------------------------------------------------------------------------------|---------------------------------------------------------------------------------------------------------------------------------------------------------------------------------------------------------------------------------------------------------------------------------------------------------------------------------------------------------------------------------------------------------|
| 1. What is your relationship to this person (Check all that apply)                    |  1. A stranger, someone you met for the first time
 2. Someone you knew, but not closely
 3. A close friend, someone you knew very well
 4. A sexual partner
 5. A family member
 6. A dealer
 7. Other _____ |  1. A stranger, someone you met for the first time
 2. Someone you knew, but not closely
 3. A close friend, someone you knew very well
 4. A sexual partner
 5. A family member
 6. A dealer
 7. Other _____ |  1. A stranger, someone you met for the first time
 2. Someone you knew, but not closely
 3. A close friend, someone you knew very well
 4. A sexual partner
 5. A family member
 6. A dealer
 7. Other _____ |
| 2. How long have you known this person?                                               |  1. Less than 6 months
 2. 6 months to 1 year
 3. 1-2 years
 4. 3-6 years
 5. More than 6 years                                                                                                                                                                     |  1. Less than 6 months
 2. 6 months to 1 year
 3. 1-2 years
 4. 3-6 years
 5. More than 6 years                                                                                                                                                                     |  1. Less than 6 months
 2. 6 months to 1 year
 3. 1-2 years
 4. 3-6 years
 5. More than 6 years                                                                                                                                                                     |
| 3. Did this person know your recruiter, that is, the person who gave you your coupon? |  1. Yes
 2. No
 3. Don't know                                                                                                                                                                                                                                                                                             |  1. Yes
 2. No
 3. Don't know                                                                                                                                                                                                                                                                                             |  1. Yes
 2. No
 3. Don't know                                                                                                                                                                                                                                                                                             |

6. How many coupons have you refused to accept? \_\_\_\_\_

**APPENDIX 11. RDS Coupon Example**

|                   |                                                                                                                                                                                                                                                     |
|-------------------|-----------------------------------------------------------------------------------------------------------------------------------------------------------------------------------------------------------------------------------------------------|
| Coupon #
00102 | Site:

Date/Hours

3:30 pm-7:30 pm Monday-Friday

8am 4 pm Saturday

Please keep this ticket!

Address:

Telephone:

ID #: _____

Activation Date: __/__/__

Expiration Date: __/__/__ |
| Coupon #
00102 | Site:

Date/Hours

3:30 pm-7:30 pm Monday-Friday

8am-4 pm Saturday

Give this to a friend

Address:

Telephone: ???

ID #: _____

Activation Date: __/__/__                                 |

**Expiration Date:** \_\_/\_\_/\_\_

**APPENDIX 12. Data Corrections Log**

**Data Corrections Log**

(This form will be translated and back-translated by different translators to Portuguese.)

**PROGRAMMATIC MAPPING AND HIV PREVALENCE STUDY IN ANGOLA**

| Interview
Date | Event
# | Venue
ID | Interviewer
ID | Survey
ID | Problem | Correction | Initials |
|---------------------------|--------------------|---------------------|---------------------------|----------------------|----------------|-------------------|-----------------|
|                           |                    |                     |                           |                      |                |                   |                 |
|                           |                    |                     |                           |                      |                |                   |                 |
|                           |                    |                     |                           |                      |                |                   |                 |
|                           |                    |                     |                           |                      |                |                   |                 |
|                           |                    |                     |                           |                      |                |                   |                 |
|                           |                    |                     |                           |                      |                |                   |                 |
|                           |                    |                     |                           |                      |                |                   |                 |
|                           |                    |                     |                           |                      |                |                   |                 |

**APPENDIX 13. Population Size Estimation Contact Log**

Population Size Estimation Contact Form

Page \_\_\_\_\_ of \_\_\_\_\_

*(This form will be translated and back-translated by different translators to Portuguese.)*

**PROGRAMMATIC MAPPING AND HIV PREVALENCE STUDY IN ANGOLA**

|                                                                        |                                                          |                                                          |                                                          |                                                          |                                                          |
|------------------------------------------------------------------------|----------------------------------------------------------|----------------------------------------------------------|----------------------------------------------------------|----------------------------------------------------------|----------------------------------------------------------|
| 1. Date                                                                | ___/___/09                                               | ___/___/09                                               | ___/___/09                                               | ___/___/09                                               | ___/___/09                                               |
| 2. Distribution site                                                   |                                                          |                                                          |                                                          |                                                          |                                                          |
| 3. Time of distribution                                                |                                                          |                                                          |                                                          |                                                          |                                                          |
| Demographic Information:                                        |                                                          |                                                          |                                                          |                                                          |                                                          |
| 4. Age (If <18 years old, do not give object.)               |                                                          |                                                          |                                                          |                                                          |                                                          |
| 5. Living in _____ (If no, do not give object.)                 |  Yes  No |  Yes  No |  Yes  No |  Yes  No |  Yes  No |
| 6. Is a female sex worker (If no, do not give object.)          |  Yes  No |  Yes  No |  Yes  No |  Yes  No |  Yes  No |
| Unique Object Distribution:                                     |                                                          |                                                          |                                                          |                                                          |                                                          |
| 7. Have already received [object] (If yes, do not give object.) |  Yes  No |  Yes  No |  Yes  No |  Yes  No |  Yes  No |
| 8. Accepted [object]                                                   |  Yes  No |  Yes  No |  Yes  No |  Yes  No |  Yes  No |

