#### *Inclusion Criteria for PLACE*

Male and female participants who meet the following eligibility criteria will be invited to participate in the project:

- At least 15 years of age at time of interview and not accompanying or running an errand for parents
- Recruited at selected venues
- Consent to participant in a face-to-face structured behavioral survey and provide written informed consent with initials or an X

Additionally participants that meet one of the following inclusion criteria for key populations will be offered additional STI testing:

- At least one sexual contact for cash in the last 12 months
- Man or transgender woman that has had oral or anal sex with another man in the past 12 months
- Identification as a male-to-female transgender woman

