##### ***Inclusion Criteria***

For the Cabinda study, female participants who meet the following eligibility criteria will be invited to participate in the project:

- At least one sexual contact for cash in the last 12 months
- At least 15 years of age at time of interview
- Resident of Cabinda province at time of interview
- Possession of a valid RDS coupon
- Consent to participate in a face-to-face structured behavioral survey

The interviewer will explain the study to the participant and ask for written informed consent (Appendix 9).

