## **Assumptions**

Members of the sex worker, MSM or transgender population must have a chance of being included in both sources of data. Data from both sources will be evaluated for any potential barriers to inclusion of members of the target population. Where this assumption is violated, this will be clearly documented and reported, and other sources of data will be considered.

The multiplier method requires clear and consistent population definitions, time reference periods, and catchment areas between the different data sources. During preparation for implementation of multiplier activities and collection of unique object and survey data, these issues will be carefully considered, and investigators will ensure that definitions across data sources will be coordinated.

**Objective 8: To provide data to inform and guide future behavioral surveys and prevention strategies targeting sex workers, MSM or transgender women in Angola.**

Responses collected at a roundtable meeting with key stakeholders held at the end of data collection will be analyzed. We will invite all USG agencies, local NGOs, and key government officials to discuss how survey results can assist ongoing and future behavioral activities targeting sex workers, MSM and transgender women and how these results can advance priorities outlined in the Country Operating Plan (COP) and Angola's National Strategic Plan (NSP). Priorities for Local AIDS Control Efforts (PLACE) studies in identifying high transmission HIV/AIDS areas to improve HIV prevention program delivery. Combined data from objectives A, B and C will be used to guide the design of new prevention messages targeting sex workers, MSM and transgender women. All results will be shared with NGOs and other agencies working directly with sex workers, MSM and transgender women in Angola.

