| 
B7
            | 
On a busy day, how many women aged 18 and older come here as patrons (to socialize, drink alcohol, etc.) over the course of the entire day and night?
 
READ OPTIONS. CIRCLE ONE CODE BETWEEN 0 AND 13 THAT INDICATES THE CORRECT RANGE.
                                                                                                                                                                                 | 
CIRCLE ONE CODE BETWEEN 1 AND 13:
 
 
 0	1	
 
 1-14	2	
 
 15-29	3	
 
 30-49	4	
 
 50-99	5	
 
 100-149	6	
 
 150-199	7	
 
 200-299	8	
 
 300-399	9	
 
 400-499	10	
 
 500-999	11	
 
 1000-1999	12	
 
 Over 2000	13	
 
 |                                                               | 0 | 1 | 1-14 | 2 | 15-29 | 3 | 30-49 | 4 | 50-99 | 5 | 100-149 | 6 | 150-199 | 7 | 200-299 | 8 | 300-399 | 9 | 400-499 | 10 | 500-999 | 11 | 1000-1999 | 12 | Over 2000 | 13 |

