| B13        | On a busy night, how many of the _____ (NUMBER FROM B12) men aged 18 or older who come here do you think exchange sex for money? IF NONE, ENTER 0.                                                                                                                                                                           | NUMBER: _____                                                                                                                                                                                |  |
| B14        | On a busy night, how many of the _____ (NUMBER FROM B12) men aged 18 or older who come here are men who have sex with other men? These men can be gay, bisexual or straight. IF NONE, ENTER 0.                                                                                                                               | NUMBER: _____                                                                                                                                                                                |  |
| B15        | How many transgender people, transsexuals or transvestites do you estimate come here on a busy night?

IF NONE ENTER ZERO. IF THE PERSON DOES NOT KNOW CIRCLE 999.

SOME PEOPLE ARE BORN MALE , BUT LATER ON IN THEIR LIVES MIGHT NOT SEE THEMSELVES AS A MAN. THEY MAY FEEL MORE COMFORTABLE AS A WOMAN. | NUMBER: _____

DON'T KNOW   999                                                                                                                                                        |  |

| B16 | Some people inject drugs illegally. These people need health care services. About how many of the men who come here on a busy day do you think may have injected drugs in the past year? Would you say....
READ OPTIONS | 
NONE 0
 
VERY FEW 1
 
FEW 2
 
LESS THAN HALF 3
 
ABOUT HALF 4
 
MORE THAN HALF 5
 
ALMOST ALL 6
 
ALL 7
 
DON'T KNOW 9
                                                                      |

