### Instructions for using Size Estimation Field Staff Contact Log

- 1. Date:** Write the date of distribution activity.
- 2. Distribution Site:** Write the site in which the distribution activity is taking place.
- 3. Time:** Write the time of distribution activity.
- 4. Age:** If the person is under 15 years old, do not give object or collect any other information.
- 5. Living or working in Cabinda Province:** Ask question: *Do you live or work in Cabinda province?* If answer is no, do not give object or collect any other information.
- 6. Is a female sex worker:** Ask question: *In the past 12 months, have you had received money for sex?* If answer is no, do not give object or collect any other information.
- 7. Have already received [object]:** Ask question: *Have you received a [object] by a field staff member in the past two weeks?*
- 8. Accepted [object]:** Explain that these objects are being distributed for a survey and that the only participation needed from him in this survey is to accept the object and that no other questions will be asked. If the person accepts the object, ask him to keep the object because in about two weeks to four months, someone might ask them again if they have received this object.

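### The size-estimation forms and the survey documents do not share one age limit: some use 15, some 18, and some none

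*Protocol*

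**What the plan says.** Eligibility in the body of the protocol is 15 or older:

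- Cabinda RDS, Inclusion Criteria (VI.D): "At least 15 years of age at time of interview".
- PLACE, Inclusion Criteria (VI.C, Step 4): "At least 15 years of age at time of interview and not accompanying or running an errand for parents". The consent section for venue patrons and workers gives participants aged 15-17 their own consent procedure, so enrolling them is deliberate.
- Study Populations (VI.B) also starts at 15. However, the sex-worker definition quoted there leaves out people under 18.

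The forms differ:

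- Appendix 13, printed object log, item 4: after a less-than sign, "18 years old, do not give object".
- Appendix 13, instructions for that same item: "If the person is under 15 years old, do not give object or collect any other information".
- Appendix 3, Form B, item B7, the base for the sex-work items B9 and B10: "how many women aged 18 and older come here as patrons". B13 asks how many "men aged 18 or older who come here do you think exchange sex for money", and B14 how many "men aged 18 or older who come here are men who have sex with other men".
- Form B, items B5-B6 (women working at the site) and B15 (transgender people): no age limit.
- Appendix 4, Form C, Q12: the interview stops if the respondent is under 18.

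Two lesser places also disagree. RDS recruiters are told to invite people over 15, where the criterion says at least 15, and the Appendix 6 refusal list offers being under 18 as a reason.

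The Assumptions section in VIII.C states what the Cabinda method needs: "The multiplier method requires clear and consistent population definitions, time reference periods, and catchment areas between the different data sources". It also requires that members of the population be able to enter both sources.

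**The concern.** The sizes are meant to serve as denominators for programme coverage and as inputs to epidemic projections (VIII.C). A denominator has to describe the same people as the indicator it is used with.

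In Cabinda, a worker who follows the printed log gives 15-17-year-olds no chance of an object, although the survey that supplies the second count admits them. That breaks the protocol's own multiplier assumptions. It also makes it impossible to reach everyone who meets the study definition, which is the stated aim of distribution. If some staff follow the form and others the instructions, the number of objects given out has no single definition.

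In the PLACE provinces, the size is a sum of site counts. The female sex worker total adds patrons counted from 18 to workers counted at any age. Form B asks whether girls aged 15-17 come to the site (B4, item H) and then leaves them out of the patron count.

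**Working it through.** The protocol gives no figure for this point, so there is none to reproduce. The share of each key population aged 15-17 is not stated. Call it s and treat it as an assumption.

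**PLACE patron counts (B7 with B9-B10, B13, B14).** A count limited to 18+ covers 1 - s of the 15+ population:

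| s (assumed) | 5% | 10% | 20% | 30% |
|---|---|---|---|---|
| counted / 15+ | 0.95 | 0.90 | 0.80 | 0.70 |

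The correction for visits to several sites (VIII.C, step 7) is linear in the site-level total, so for given values of its two other inputs a proportional shortfall passes straight through. A coverage ratio with a 15+ numerator over such a size would be too high by 1/(1 - s): 1/0.95 = 1.05 at s = 5% and 1/0.80 = 1.25 at s = 20%.

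**Female sex workers in total.** Let P be the number aged 15+ who are patrons and W the number who are workers. Form B yields (1 - s)P + W, plus any workers under 15, because B5-B6 set no floor. Leaving those aside, the shortfall is sP/(P + W). With P = W and s = 10%, for illustration, it is 0.10 x 0.5 = 5%. The result is neither a 15+ nor an 18+ total.

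**Cabinda multiplier.** The protocol's estimator is n1 x n2 / m, where n1 is the number given objects, n2 the RDS participants and m those in both. Suppose the printed log is followed, the true 15+ size is N, and s' is the share of RDS participants aged 15-17.

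- Adults number N(1 - s), and a fraction n1 / [N(1 - s)] of them hold an object.
- Only the adult part of the RDS sample can hold one, so the expected m is n2 (1 - s') n1 / [N(1 - s)].
- The estimate is therefore N(1 - s)/(1 - s').

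With s = 15%:

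- s' = 15% gives 0.85/0.85 = 1.00 of the true size.
- s' = 5% gives 0.85/0.95 = 0.895.
- s' = 0 gives 0.85, which is exactly the 18+ size.

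Now let r be the recruitment rate of minors relative to adults. Then s' = sr/(1 - s + sr), and the estimate becomes N[1 - s(1 - r)]. Take N = 1,000 (assumed), n2 = 400 (the planned RDS sample) and n1 = 400 (the protocol wants at least as many objects as the sample). Simulated means over 2,000 repeats are in brackets; the last column was simulated with r = 0.001:

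| s | r = 1 | r = 0.5 | r = 0 |
|---|---|---|---|
| 10% | 1,000 (1,004) | 950 (957) | 900 (903) |
| 20% | 1,000 (1,001) | 900 (916) | 800 (802) |

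The simulated values at r = 0.5 are somewhat higher mainly because drawing 400 of 1,000 without replacement weakens the under-recruitment. With a 15+ rule in both sources, and objects equally likely to reach minors and adults, the formula returns 1,000 for every s and r tried.

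**The case against.** The strongest reply is to compare form with form. Form C stops below 18, so if the instruments are used as printed, the PLACE interviews and the patron counts are both adult-only, and the conflict is with the eligibility text. That stands, and it matters for the remedy: moving Form B alone to 15 would set 15+ sizes against an 18+ interview. It does not remove the problem, because B5-B6 and B15 have no floor under either reading.

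Three stronger claims are tempting. The documents support none of them.

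- A reader might infer that the size forms admit adults only. They do not: B5-B6 and B15 are unlimited, and the log's instructions say 15.
- A reader might infer that the Cabinda estimate must be too low. It is not if RDS recruits minors in proportion. If RDS recruits none, the estimate is a sound 18+ size with the wrong label.
- A reader might infer that every coverage indicator is inflated. Most coverage rows in Table 4 divide by the number interviewed, so the size does not enter them.

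Other points in the plan's favour are fair. The log looks partly like an unedited template, with a pre-printed year and a blank place name. Operational definitions may still be set by the readiness assessment or during analysis. The Assumptions section commits the investigators to coordinating definitions. VIII.C also plans an allowance for people missing from the PLACE count, though it does not mention minors. None of this tells field staff which printed age to apply.

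**Conclusion.** The age limits contradict each other and need correcting before the forms are used. It is certain that the object log disagrees with its own instructions, that Form B mixes 18+ items with items that have no floor, and that Form C and the quoted sex-worker definition conflict with 15+ eligibility.

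The numerical effect is conditional. PLACE patron sizes fall short of the stated 15+ population by the share aged 15-17, which the documents do not give. The Cabinda estimate lies between the 15+ and the 18+ size, depending on how well RDS reaches minors, provided all staff apply the printed 18 rule and holding an object is otherwise unrelated to RDS recruitment. If staff apply different cut-offs, it has no single target population.

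**What to change.** Set one age definition and carry it through the study-population text (VI.B), Form B (B5-B7, B13-B15), Form C Q12 and both parts of Appendix 13. For consistency, also align the RDS recruiter instruction and the Appendix 6 refusal option.

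- **If the stated 15+ criterion is kept:** change the log item to under 15, the Form B items to 15 and older, and the Form C stop to under 15, all at the same time. B5-B6 and B15 should state the same floor.
- **If adult-only counts are kept:** add an 18+ limit to B5-B6 and B15, correct the log's instructions, restrict n2 and m in the multiplier to participants aged 18+, and label the sizes and the indicators used with them as 18+.

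Either way, keep the age recorded on the object log in the entered data. The listed data elements are only number, place and time, and age would allow n1 to be restricted later.

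The cost is a few form edits before translation and programming. The drawback of the 15+ option is that venue informants may guess less well about ages 15-17. After fieldwork, the omitted patron counts cannot be recovered.
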